**Phase 2 – Weeks 5-11 – conditioning**						
Cardio (aerobic)	Freestyle aerobics set to music	Antero-postero movements	As for Phase 1 plus	4-5/10 RPE and 126-128 bpm music		Participant sets own pace as able
		Lateral movements	Zig zag movements			
		Multiple direction changes	Knee lifts			
			Lateral lower body with			
		Increased strength component	antero-postero upper body			
		Arm movement	movements			
		Non-isodirectional upper and lower limb movements				
Strength	Circuit	All major muscle groups	Different stations	Recommended RPE = 4-5/10 2x 30 second intervals per station	Increase weights as able	Remove/reduce weights
		Compounded exercise	including:			
			Continuous rolling movement on mat			Substitute wrist or ankle weights as necessary.
			Fitball squats			
			Weighted bag drags			
			Ball bouncing			
Balance	Circuit	Static and dynamic balance	Heel-toe (walk the line) One-leg pose with ball throws	2x 30 second intervals per station	Challenges to concentration	One-to-one supervision or remove element (e.g. ball throws)
Coordination Agility	Free style aerobics + Circuit + Group	Circuit:	Circuit:	Circuit:	Faster movements as able	One-to-one supervision and reduce speed of movement
Reaction time		Dynamic combination/compounded exercises	Flat foot heel drumming	2x 30 second intervals per station	Substitute smaller balls	
		Group:	Walking ball bounces		Alternate between dominate & non-dominate hands	
		Dynamic knee lifts alternating with rapid foot movements	Group:			
			Various moving foot sequences			
			Catch dropping objects (noodle drops)			
Flexibility + warm down	Circuit + Group	Circuit: Spinal rotation	Circuit: Alternating wall taps	Circuit: 2x 30 second intervals	Increase according to tolerance & musculo-skeletal status	Decrease with musculo-skeletal status
		Group: Static stretches on floor	Group: Cat and camel stretches	Group: 3-4/10 RPE Minimum 20 s		
			Lying hamstring stretches			
			Back extensions			
**Phase 3 – Weeks 12-16 – conditioning**						
Cardio (aerobic)	Freestyle aerobics set to music	Antero-postero movements	As for phases 1 and 2 plus:	5-6/10 RPE and 126-128 bpm music	Participant sets own pace as able (increases as able)	Participant sets own pace (decreases intensity or complexity of movement as required)
		Lateral movements	‘Pride of Erin’ dance steps			
		Multiple direction changes	Marching with alternating parallel and 45 degree angle arm movements			
		Increased demands on postural control				
		Higher arm movement				
		Non-isodirectional upper and lower limb movements				
Strength	Circuit	All major muscle groups	Lunges	Recommended RPE = 5-6/10 2x 40 second intervals per station	Increase weight as able	Remove/reduce weight or substitute exercises targeting same muscle group as tolerated
		Compounded exercise	D/b flyes supine on roller Modified (wall) push ups			
Balance	Circuit	Static and dynamic balance	Stand on foam	2x 40 second intervals per station	Introduce perturbation/reduce base of support	One-to-one supervision or remove element (e.g. ball throws)
			Step onto foam and assume one leg pose			
			One legged stand and reach			
Coordination Agility	Free style aerobics + Circuit + Group	Circuit:	Circuit:	Circuit:	Faster movements as able	One-to-one supervision and reduce speed of movement
Reaction time		Dynamic combination exercises	Noodle drops	2x 40 second intervals per station		
		Group:	Group:			
		Dynamic knee lifts in combination with rapid foot movements	Freestyle aerobic routine + noodle			
Flexibility + warm down	Circuit + Group	Circuit: Spinal rotation	Circuit: Alternating wall taps	Circuit:	Increase with musculo-skeletal status	Decrease with musculo-skeletal status
		Group: Static stretches on floor	Group: Cat and camel stretches	2x 40 second intervals per station		
			Lying hamstring stretches			
			Back extensions			
			Quadruplex			

Strength training incorporates progressive weight training and weight bearing exercises involving the major muscle groups. Motor training involves both static and dynamic balance, coordination and agility requiring manoeuvring around and stepping over objects. Reaction time training includes ball activities and flexibility training involves dynamic and static stretches for all major muscle groups (See Table 2). Sessions are conducted by accredited fitness instructors, with a maximum of 20 participants and an instructor-to-participant ratio of 1:10.

### Control group

The control group is on a waiting list to attend the 16-week exercise program which commences at the end of the study; and after the post intervention measures have been completed by both groups. The classes are offered free of charge. Control group participants are contacted by telephone every 4 weeks to foster an ongoing sense of engagement in and relevance to the study.

### Intervention fidelity

Two instructors are present in each class. Only these two instructors will administer the intervention. At random intervals an independent assessor will observe all classes and monitor for content consistency using a check-list based on the explicit components of the exercise intervention protocol. In addition, instructors will maintain a log of activities in each class and these logs will also be reviewed by the independent assessor to check for intervention fidelity.

### Adherence to intervention protocol

Trained fitness instructors document attendance at each class. Intervention group are asked to plan to attend at least 85% of classes and are followed up by telephone if they are absent for two consecutive classes. In order to maximise participant contact and follow-up participants in both groups are asked to provide at least two sets of contact details; direct and via a friend or family member.

### Assessment protocol

#### Screening

Information sessions about the study are conducted at a number of local organisations that are attended by older adults. Individuals who express interest in the study at the information sessions are asked for their contact details and initial checks of age group and the ability to walk 20 meters unaided are completed. Individuals with preliminary eligibility are issued with General Medical Practitioner (GP) clearance forms which are subsequently used should the screening telephone interview reveal the requirement for GP clearance.

The formal screening process is conducted by telephone and takes approximately 15 minutes. It includes the TICS and the Pre-Activity Readiness Questionnaire (PAR-Q)[27]. Individuals who are otherwise eligible and who report a serious medical condition are asked to take clearance forms to their GPs to obtain written permission to participate. Once individuals have been assessed as being eligible to participate they are invited to attend a data collection and randomisation session where demographic and health information is collected along with baseline outcome measures.

### Baseline demographics, current activity levels and health information

Details of age, education, marital status, occupation and language used at home are collected by interview. Participants are asked to give details of any medical conditions that may affect physical activity (using the PAR-Q). They are asked to complete the 21 item Depression, Anxiety and Stress Scale (DASS-21) which has good internal consistency as well as convergent and discriminant validity, especially for the depression scale [28]. In addition, all participants will be fitted with a pedometer for five days to record activity levels at baseline.

### Outcome measurement

The primary outcome measure is neurocognitive test performance related to the processes of working memory, inhibition, shifting, verbal fluency and simple and complex reaction time i.e. executive function. These functions are highly associated with age-related cognitive decline, mobility and the ability to perform activities of daily living [29-31]. A recent randomised controlled trial of a resistance training program used similar primary outcome measures and demonstrated an effect for a twice a week exercise program [32]. The secondary outcome measures are blood serum levels of BDNF, physical and functional capacity including the 6 minute walk test, the ‘timed up and go’ test and the one-leg stance test of balance; and anthropometric values related to girth circumference at the waist and hip, resting heart rate and blood pressure.

Physical functioning and cognitive assessment are conducted in the community (in halls) by exercise physiologists and psychologists, respectively. Anthropometric measurements are completed by a registered nurse. Cognitive testing requires less than 60 minutes and precedes physical assessment which lasts for 30–40 minutes. Participants are transported to an accredited blood collection facility. Blood samples are then conveyed to a laboratory for assay of plasma Brain Derived Neurotrophic Factor (BDNF).

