### Sample size

One hundred participants will be recruited for the study. Sample size is determined using a power calculation to detect between group differences in the primary outcome measures. Previous randomised controlled trials of exercise interventions have shown effect sizes between 0.24 and 1.17, in similar populations, for cognitive performance outcome measures, as a result of aerobic interventions [7]. To obtain 80% statistical power with an α level of 0.05, using a t-test for two independent groups and an effect size of 0.6, the sample size required in each of the two groups is 36 participants (G*Power 3.1) [25,26]. Samples of 50 for both the intervention and control groups are recruited, to allow for attrition.

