### Primary outcome measures

#### Neurocognitive Tests

##### California older adult stroop test (inhibition)

Stroop tests assess the ability to suppress a habitual response in favour of an unusual response [33,34]. They generally demonstrate good test-retest reliability (0.90, 0.83 and 0.91 for the three parts of the test) [35] and minimal susceptibility to practice effects [36]. The COAST is a Stroop test developed specifically for use with older populations [37]. Participants are required to first name colours (Colour), then read colour name words (Word); and then name ink colours when the names of colours are printed in a different (non-corresponding/incongruent) colour ink. During the incongruent condition, the two conflicting sources of colour information cause a competing effect (Interference) which is most typically observed as a prolonged reaction time compared to the neutral or congruent conditions [38].

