##### Controlled oral word association test (COWAT) (verbal fluency)

Different forms of the COWAT test measure verbal fluency and also draw on executive function and memory. Participants are given one minute to generate as many words as possible that begin with a specific letter. This task is repeated three times with three different letters (e.g. F, A, S). These tests generally demonstrate inter-scorer reliability of 0.70, retest reliability of 0.88 and concurrent validity [39].

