##### Letter-number sequencing test (LNS) (working memory)

The Letter-Number Sequencing test [40] measures working memory as well as sequencing, attention and concentration abilities. The participant is read a combination of numbers and letters and is asked to recall the numbers first in ascending order and then the letters in alphabetical order. Each item consists of two trials, and each trial is a different combination of numbers and letters. There are seven items ranging from 2-letter/number sequences (e.g., B-7) to 8-letter/number sequences (e.g., S-2-L-8-B-1-G-7). The maximum score possible is 24 points. The validity and reliability of this test is well established in older adults with test-retest reliability in the range of 0.70 to 0.80 and a factor loading of 0.62 with the Working Memory Index [41].

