##### Psychomotor speed (simple reaction time and complex reaction time)

Reaction Time, the time between presentation of a stimulus and initiation of a response, is said to reflect psychomotor and processing speed; and is assessed with 1-choice and 4-choice stimulus conditions. Using computer based testing the first stimulus condition requires identification of a single object (e.g., yellow circle). The second stimulus condition requires the discrimination of a single object, amongst 4 object choices. Simple reaction time (SRT) and 4-choice reaction time (CRT) are calculated as the time (milliseconds) from perception (release of press-pad) to touch of appropriate stimulus on the screen. Split half reliability of up to 0.90 has been reported for an 18 task trial [35]

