##### Trail making test (TMT) (part A & B) (executive function and shifting)

The TMT is considered to be a test of visual search, attention, flexibility of thinking, motor function, and executive function [34,36,39]. Part B of the TMT requires the individual to mentally shift between two well-rehearsed sequences (numbers and letters) as quickly and as accurately as possible. Shifting ability represents the capacity to adapt to changes in the environment by switching from one mental set to another.

In Part A, the task is to connect the numbers in ascending order (i.e.1-2-3-4…). Part B involves alternately connecting numbers and letters in ascending order (for the numbers) and sequential order for the alphabet letters (i.e. 1-A-2-B…). The score derived for each trail is the number of seconds required to complete the task [39]. Reliability tests for the TMT range from 0.60 to 0.90 [41] and the test is particularly useful for detecting early stages of dementia [41].

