### Analyses

The data analysis for the randomised controlled trial will be undertaken on an intention-to-treat basis. To characterize the sample in this study, means or proportions and standard deviations (SDs) will be calculated by randomisation group for multiple baseline demographic, cognitive functioning and anthropometric variables. Unadjusted means and SDs for each cognitive performance measure obtained at the baseline and follow-up visits will be calculated. Missing outcome data will be imputed using multiple imputation [52]. Analysis of covariance will be undertaken for 16 week follow-up outcome measure scores, controlling for baseline cognition (TICS), and using baseline outcome values as covariates. Ninety- five per cent confidence intervals and effect sizes (standardised mean differences) will be calculated for each outcome measure. Differences in follow-up secondary outcome measure scores will be assessed for normality of distribution and either parametric or non-parametric statistical analyses applied as appropriate (e.g. ANCOVA, logistic regression etc.). Hierarchical multiple regression analyses will be used to investigate associations between plasma BDNF levels and a range of independent variables including demographic, anthropometric, cognitive functioning and physical functioning variables.

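### Six or seven co-equal primary cognitive scores are sized on one undivided alpha of 0.05 and analysed separately, so the 5% error rate does not cover a general claim of improved cognition

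*Protocol article*

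**What the plan says.** All references are to the protocol article.

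- **Outcome measurement** speaks of one primary outcome measure but defines it as "neurocognitive test performance related to the processes of working memory, inhibition, shifting, verbal fluency and simple and complex reaction time". That is six named processes.
- **Primary outcome measures** describes five instruments:
  - The California Older Adult Stroop Test (COAST), headed as a test of inhibition, has three parts: "Participants are required to first name colours (Colour), then read colour name words (Word"), followed by the incongruent condition that gives Interference.
  - For verbal fluency (COWAT), "This task is repeated three times with three different letters".
  - For Letter-Number Sequencing (LNS), "The maximum score possible is 24 points".
  - For psychomotor speed there are two scores: "Simple reaction time (SRT) and 4-choice reaction time (CRT) are calculated as the time (milliseconds").
  - For the Trail Making Test (TMT), Parts A and B, "The score derived for each trail is the number of seconds required to complete the task". The text ties shifting to Part B.
- **Sample size** uses the plural: "Sample size is determined using a power calculation to detect between group differences in the primary outcome measures". It gives one alpha of 0.05, 80% power and an effect size of 0.6. This leads to 36 required per group and 50 recruited per group to allow for attrition.
- **Analyses**: "Analysis of covariance will be undertaken for 16 week follow-up outcome measure scores", with a 95% confidence interval and a standardised mean difference for each outcome measure.

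The article names no lead score, composite, testing order, all-must-succeed rule or adjustment.

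**The concern.** The article places several cognitive scores on an equal footing as primary and sizes them as if there were only one. The Abstract's Discussion then looks ahead to one general conclusion, that multimodal exercise improves cognitive performance in later life. If a single nominally significant score were taken to support that conclusion, its error rate would be that of the whole set of tests, well above 5%. A false positive on one test could then be reported as a cognitive benefit of the programme.

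The other side of the problem is power. The stated 80% belongs to one score tested at the full 0.05. Once the alpha is shared across the scores, neither the 36 required nor the 50 recruited per group gives 80% for each score on the t-test used for planning.

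**Working it through.** **1. The plan's own figure.** Inputs from Sample size: d = 0.6, alpha 0.05, power 80%, two-group t-test, sidedness not stated. The exact noncentral-t calculation gives 36 per group one-sided (power at 36 is 80.9%) and 45 per group two-sided (power at 36 is 70.9%). The stated 36 therefore reproduces as one score tested one-sided at 0.05. No allowance for several scores is in it.

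**2. Counting the primary scores.** COAST Interference 1, COWAT 1 (three letters summed, an assumption), LNS 1, simple reaction time 1, complex reaction time 1, TMT B 1. That makes six, one per named process. TMT A makes seven.

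**3. Chance of at least one false positive, independent scores, 0.05 each.** Formula: 1 − 0.95^k.
- k = 6: 1 − 0.95^6 = 26.5%
- k = 7: 1 − 0.95^7 = 30.2%

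**4. Correlated scores.** The article gives no correlations between the tests, so a common pairwise correlation r is assumed. With c the critical value and z standard normal, the chance for two-sided tests is

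1 − E{[Φ((c − √r·z)/√(1−r)) − Φ((−c − √r·z)/√(1−r))]^k},

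evaluated by quadrature. For one-sided tests the second Φ term is dropped.

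| Quantity | r = 0 | 0.3 | 0.5 | 0.7 |
|---|---|---|---|---|
| 7 scores, two-sided 0.05, any false difference | 30.2% | 27.1% | 23.0% | 17.8% |
| 6 scores, two-sided 0.05, any false difference | 26.5% | 24.1% | 20.7% | 16.4% |
| 7 scores, two-sided 0.05, false benefit only (nominal 2.5%) | 16.2% | 13.7% | 11.5% | 8.9% |
| 7 scores, one-sided 0.05, false benefit (nominal 5%) | 30.2% | 24.5% | 20.3% | 15.9% |

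The independent false-benefit figure in the third row is 1 − 0.975^7 = 16.2%.

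**5. What adjustment costs.** Full Bonferroni over seven, which is also the first Holm step, gives 0.05/7 = 0.00714 per score. For ANCOVA the effect is d/√(1 − ρ²), with ρ the assumed correlation between baseline and follow-up: 0.6/√0.75 = 0.693 at ρ = 0.5 and 0.6/√0.51 = 0.840 at ρ = 0.7. Two-sided power per score:

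| Analysed per group | t-test | ANCOVA, ρ = 0.5 | ANCOVA, ρ = 0.7 |
|---|---|---|---|
| 50 | 60% | 76% | 92% |
| 36 | 42% | 57% | 78% |

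On the t-test, 80% power per score at 0.00714 needs 72 per group two-sided, or 62 one-sided.

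**The case against.** **The analysis plan is not shown.** A multiplicity procedure and a rule for success are often left to it, and their absence from a journal article would not by itself be a finding. That is fair. What remains is what the article does fix: several co-equal primary scores, a sample size for those measures in the plural on one undivided alpha, and a separate analysis of each.

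**Testing each score at 0.05 is partly inference.** The 0.05 appears only in Sample size. Analyses sets no significance threshold and promises 95% intervals and effect sizes. Nor does the article say that one positive score is enough. This stands, so the error rates above are conditional on that use of the results.

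**Stronger readings that the article does not support:**
- A reader might infer an 18% to 30% chance of a false cognitive *benefit*. With two-sided tests that range counts false harm as well, and false benefit alone is about 9% to 16%. With one-sided tests, which the 36 per group implies, false benefit is about 16% to 30% against 5%, but the article does not state sidedness.
- A reader might count nine scores by adding the Colour and Word parts of COAST, giving 37% under independence. The article heads COAST as inhibition and describes Interference as the competing effect, so it does not establish those two parts as separate endpoints.
- A reader might object that reaction time is grouped under executive function. That is a matter of labelling and has no bearing on the error rate.

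**Conclusion.** The point holds in conditional form. The article makes six or seven cognitive scores co-equal primaries, sizes them on one undivided 0.05 and analyses them one by one. Followed as written, this leaves a general claim of improved cognition without 5% error control.

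The size of the problem is the range in the first three rows of the table under step 4. At the upper end, under independence, the chance of any false difference among seven scores is about six times the nominal 5% (30.2/5 = 6.0), and it remains more than three times nominal at r = 0.7 (17.8/5 = 3.6). The two-sided false-benefit figures bear nearly the same ratios to 2.5%.

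Three assumptions carry this: each score is tested at 0.05, any one positive score is read as success, and the pairwise correlations lie between 0 and 0.7. None of the three is stated in the article. The independence figures are the only ones that use no assumed positive correlation.

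**What to change.** Either of two changes would do, made before any comparison by group.

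1. **Keep the separate tests.** Fix the score or scores from each listed test that count as primary (COAST Interference, COWAT total, LNS, simple and complex reaction time, TMT B, and TMT A only if intended). Apply Holm across them, and state that the 80% power in Sample size applies to a single unadjusted score only.
2. **Use one composite.** Pre-specify a single standardised composite covering every process named in Outcome measurement, including simple and complex reaction time, with all components signed so that higher is better. Test it by the planned ANCOVA at 0.05 and report the individual tests as supportive. Leaving reaction time out would redefine the outcome that the article declares.

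Both use data already collected and need only wording, plus one derived variable for the composite. The cost of Holm is power per score, as shown in step 5. The figures for 50 per group assume no attrition, so those for 36 are the more cautious guide. Later Holm steps are less strict than the first. The composite keeps the full 0.05 and needs no more participants for multiplicity, but it dilutes an effect confined to one domain.
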